## Abstract

Total hip replacement (THR) and total knee replacement (TKR) are among the most common elective surgical procedures. There is a large consensus on the importance of physical activity promotion for an active lifestyle in persons who underwent THR or TKR to prevent or mitigate disability and improve the quality of life (QoL) in the long term. However, there is no best practice in exercise and physical activity specifically designed for these persons. The present protocol aims to evaluate the efficacy and safety of an exercise program (6 month duration) designed for improving quality of life in people who had undergone THR or TKR. This paper describes a randomized controlled trial protocol that involves persons with THR or TKR. The participant will be randomly assigned to an intervention group or a control group. The intervention group will perform post-rehabilitation supervised training; the control group will be requested to follow the usual care. The primary outcome is QoL, measured with the Short-Form Health Survey (SF-36); Secondary outcomes are clinical, functional and lifestyle measures that may influence QoL. The results of this study could provide evidence for clinicians, exercise trainers, and policymakers toward a strategy that ensures safe and effective exercise physical activity after surgery.

## 1. Introduction

Total hip replacement (THR) and total knee replacement (TKR) are among the most common elective surgical procedures [1,2,3,4]. Osteoarthritis is the most common underlying condition for both THR and TKR. A large body of published evidence has consistently shown that these surgical procedures successfully decrease pain and improve mobility and quality of life [5,6].

The utilization rates of THR and TKR procedures have been increasing in the last 2–3 decades due to technical surgical improvements, significant benefits obtained, and the populations increased longevity. This volume growth poses an increasing economic burden in healthcare systems in terms of hospitalization costs and subsequent rehabilitation [7,8]. This trend is similar in all developed countries, although the difference in these surgical procedures’ incidence may be due to variations in economic status, health care delivery systems, patient preferences, or osteoarthritis prevalence [9].

As THR and TKR relieve joint pain, this represents an opportunity for these individuals to become more physically active [10]. Regular physical activity is one of the most effective interventions to improve the prevalent chronic comorbid conditions, including obesity, diabetes, hypertension, and cardiovascular deconditioning that commonly coexist with hip and knee osteoarthritis [11]. Furthermore, as physical activity induces quadriceps hypertrophy and improves strength, it is one of the main modifiable factors in patients with knee and hip osteoarthrosis who often exhibit weakness and atrophy [12] Therefore, THR and TKR could benefit not only the overall health of the individual undergoing surgery [13,14], but also relieve symptoms by increasing physical activity.

However, individuals who have completed THR or TKR treatment (surgery plus subsequent rehabilitation phase) do not seem to increase physical activity from pre-to-post-surgery. American [15,16] and Dutch [17,18] studies, show that individuals who undergo THR or TKR tend to be older sedentary adults, and it is estimated that around 49% of them are over-weight or obese, 16% have diabetes, and about half have high blood pressure. Studies on physical activity changes due to THR or TKR are challenged by wide variability in demographics, methods used to assess physical activity, and different care pathways used across studies [13,14]. However, the studies that assessed PA from pre- to post-THR and -TKR have reported that physical activity does not change the first three months post-surgery. The results of studies with follow-up assessments longer than three months but shorter than 12 months are contradictory, and the results of follow-ups longer than 12 months provide weak evidence of increased physical activity [13,14,17,18,19]. Vissers et al. [20] reported that 4 year post-surgery patients continued to improve their perceived physical functioning, capacity, and performance of daily life activities. However, Hootman et al. [21] and Wallis et al. [22] found that persons who received THR or TKR are significantly less likely to meet WHO physical activity guidelines [23]. In addition, only 48% individuals after hip and 60% after knee replacement perform more than 7000 steps per day, respectively [21,22].

To date, there are limited data to guide orthopedic surgeons’ recommendations regarding leisure time, exercises, and sports activities after THR or TKR. Moreover, there is little evidence on the strategies to improve and maintain physical function after rehabilitation in the long term. However, it is well known that these patients have significant muscular atrophy and weakness in the affected limb that can persist for months after surgery [24], with mobility deficits remaining for many years [13,14]. Exercise programs beyond the initial post-operative rehabilitation period have been shown to reduce pain and joint stiffness, improve physical function and lessen the chance of accidental falls after surgery [25,26,27,28,29,30]. These programs have generally used strengthening exercises and functional tasks such as stair climbing to improve muscular strength and power, walking speed, and mobility. Participating in these exercise programs, persons can be physically prepared to become active again in physical activity and sport. However, a disadvantage of these programs is that persons need to exercise under clinicians’ supervision at a hospital or rehabilitation center. This makes the delivery of these programs expensive due to the high costs associated with supervised treatment and transport. In addition, some persons are excluded because of difficulties with mobility and transport to a center preclude participation [27].

Current recommendations of health-enhancing sports activities in the long term are very generic and are based on the orthopedic surgeons’ opinions [31,32,33]. The following points for exercise prescription have been evidenced. Patients should be encouraged to remain physically active to improve general health, and bone mineral density. There is evidence that increased bone quality will improve prosthesis fixation and decrease the incidence of early loosening [34,35]. Factors such as wear, joint load, intensity, and type of prosthesis must be taken into account for each subject and sport to safely recommend a specific activity after THR or TKR. It has been shown that the wear decrease is one of the main factors in improving long-term results after total joint replacement. Wear is dependent on the load, the number of steps and the material properties of joint replacements [34,35]. It is unwise to start technically demanding activities after THR or TKR, as the joint loads and the risk for injuries are generally higher for these activities in unskilled individuals [32]. Finally, it is essential to distinguish among suitable activities following THR or TKR. In order to recommend suitable physical activity after total knee replacement, it is important to consider both the load and the knee flexion angle of the peak load, while for total hip replacement, which involves a ball and socket joint, the flexion angle does not play an important role. Thus, it is prudent to be more conservative after total knee arthroplasty than after total hip arthroplasty for activities that exhibit high joint loads in knee flexion [32]. 

In conclusion, although there is a large consensus on the importance of physical function improvement to prevent or mitigate disability in persons who underwent THR/TKR in the long term, there is no best practice specifically designed to these persons. Therefore, taking into account previously published experiences [25,26,27,28,29,30] and experts’ opinion [31,32,33], we designed an exercise protocol aimed at improving quality of life (QoL) after THR and TKR for primary osteoarthritis. This goal is intended to be achieved by improving a variety of factors which influence QoL, including muscle strength, joint mobility, gait and balance function, and pain [13,14,24,25,26,27,28,29,30]. This paper presents the protocol of a single-blinded randomized trial aimed at evaluating the efficacy and safety of this exercise program. We hypothesize that after THR/TKR treatment those participating in this exercise program will have better outcomes in terms of quality of life and functional and clinical scores than persons following the usual care.

## 2. Materials and Methods

This study is carried out within the project “Physical ActIvity after hip and knee Replacement” (PAIR) and funded within the Erasmus Plus Sport program (Grant Agreement 613008-EPP-1-2019-1-IT-SPO-SCP). The study was approved by the Local Ethics Committee (Comitato Etico Indipendente di Area Vasta Emilia Centro, CE-AVEC) of the Emilia-Romagna Region (reference number AVEC: 1005/2020/Sper/IOR) and registered in ClinicalTrial.Gov (NCT04761367).

### 2.1. Study Design

The study is a randomized controlled trial. At the moment of the pre-surgery medical check-up, persons will be enrolled. After surgical treatment (THR or TKR) and subsequent rehabilitation treatment, persons will be randomly assigned to an intervention group or a control group. The intervention group will participate in a 6-month exercise program based on the PAIR exercise protocol and will receive educational sessions on the importance of maintaining an active lifestyle after THR or TKR. The control group will follow usual-care and will receive recommendations by surgeons and physiotherapist on the importance of maintaining an active lifestyle after THR or TKR. Six months after surgery, participants of both intervention and control group will be assessed before randomization (post-surgery baseline) and, subsequently, after 3 and 6 months (Figure 1).

### 2.2. Participant Recruitment

Study participation will be proposed to all patients during the pre-surgery clinical assessment (within 15 days before the scheduled day of surgical intervention) by the medical personnel of the Clinical Units Chirurgia Ortopedica Ricostruttiva Tecniche Innovative and Clinica Ortopedica e Traumatologica II of the Istituto Ortopedico Rizzoli of Bologna after verifying the presence of inclusion/exclusion criteria. Subsequently, patients will receive information about the study and will be requested to sign the informed consent form. Patients will be enrolled after signing the informed consent form.

### 2.3. Inclusion and Exclusion Procedures

During the pre-surgery assessment, the inclusion/exclusion criteria associated with age, diagnosis and comorbid conditions will be verified by a medical doctor, while criteria linked to motor function and physical activity by a professional trainer. Subsequently, criteria will be verified again at the post-surgery assessment. In this latter assessment will also be verified the presence of two additional inclusion criteria, i.e., post-surgery functional performance and pain (Table 1).

If eligible for the study, personal data (first and family name, address, telephone number(s)) will be recorded only on the informed consent form together with a study code. In all the other forms used in the study, patients will be identified with the patient’s study code.

### 2.4. Sample Size

The sample size was calculated through an a priori power analysis calculated on the study’s primary outcome, the physical health domain of the 36-item Short Form Health Survey (SF-36), assessed at post-surgery baseline and six-month assessments in both intervention and control groups. A randomized controlled pilot study in the literature with a similar rationale [36] was considered as a reference. Starting from this study, in which the SF-36 was used before and three months after the start of the intervention, was found a size effect of 1.06 (considered “increased”) with a standard deviation of 10 for each considered group. The power analysis was performed separately for THR and TKR, using a two-code test for independent groups with an error α = 0.05 and a sampling power (1-β) of 0.8, and a drop-out percentage of 30%. The minimum number required was estimated in 20 patients per group. Considering the four groups evaluated in the present study, two intervention groups (THR or TKR) and the two respective control groups, the final sample size was identified in a total of 80 patients.

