### 2.8. Statistical Analysis

The qualitative variables will be summarized in terms of frequency, and the quantitative ones in terms of mean and standard deviation for both intervention groups and control groups and for the three times of assessment. To compare characteristics between and within groups the principle of intention to treat will be used, adjusting for adherence to the exercise program. In order to compare the baseline characteristics between the two groups, the following tests will be used: Student’s t-test for parametric quantitative variables; Mann–Whitney test for non-parametric variables; Chi-square test for qualitative dichotomous variables. To compare the changes between and within intervention groups and control groups among baseline and follow-up assessments the following tests will be used: for the normally distributed variables, analyses of variance for repeated measures followed by t-test with Sidak post hoc corrections; for non-parametric variables, the Friedman test followed by the Wilcoxon test with Bonferroni correction.

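### The 80% power is calculated for an uncorrected two-group test, but the planned analysis is a repeated-measures ANOVA followed by Sidak-corrected t-tests

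*Protocol article*

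**What the plan says.** Section 2.4 (Sample Size) bases the calculation on "the physical health domain of the 36-item Short Form Health Survey (SF-36), assessed at post-surgery baseline and six-month assessments". From a pilot trial it takes the effect: "was found a size effect of 1.06 (considered “increased”) with a standard deviation of 10 for each considered group". The test is described as "using a two-code test for independent groups with an error α = 0.05 and a sampling power (1-β) of 0.8", and the allowance for loss is "a drop-out percentage of 30" per cent. The section adds that "The power analysis was performed separately for THR and TKR". Its result is: "The minimum number required was estimated in 20 patients per group". For four groups, "the final sample size was identified in a total of 80 patients". It mentions no multiplicity correction.

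Section 2.8 (Statistical Analysis) covers changes both between and within groups, across baseline and the follow-up visits. For normally distributed variables it specifies repeated-measures ANOVA and then a "t-test with Sidak post hoc corrections". For other variables it specifies a Friedman test and then Bonferroni-corrected Wilcoxon tests. It names three assessment times. It does not say how many contrasts share a correction, and it does not single out the SF-36 physical-health contrast at six months for different treatment.

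**The concern.** A power statement describes one particular test at one particular significance level. Section 2.4 gives power for a single two-sample comparison at 0.05. Section 2.8 describes an omnibus test followed by comparisons at a stricter level. Read together, the two sections leave the trial without a stated power for the analysis it says it will run.

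This matters because each joint is powered alone, with about 14 completers per arm once the planned loss has occurred. If the contrast that decides the primary question is tested at a corrected level, the chance of detecting even a difference of 1.06 standard deviations may be nearer two-thirds than four-fifths. A non-significant result in one joint could then be given more weight against the programme than the design supports.

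**Working it through.** **Inputs, all from section 2.4:** effect size d = 1.06, read as a standardised mean difference (10.6 points at SD 10); alpha = 0.05, with the garbled description of the test read as two-sided; power 0.80; drop-out 30%; 20 per group within each joint. **From section 2.8:** Sidak-corrected post hoc t-tests and three assessment times. **Assumed, because the article does not give it:** the number m of contrasts in the Sidak family.

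**Step 1: reproduce the stated figure.** Normal approximation for two means:

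n = 2(z₀.₉₇₅ + z₀.₈₀)² / d² = 2(1.960 + 0.842)² / 1.06² = 13.97, so 14 per group.

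Inflating for drop-out: 14 / (1 − 0.30) = 20. This is exactly the stated number.

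**Step 2: the same calculation by exact t.** The noncentral t distribution needs 15 completers per group for 80% power (80.0%), and 15/0.7 = 21.4, so 22. The difference from 20 is two patients per group.

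**Step 3: power after the planned loss.** 20 × 0.70 = 14 completers per group. The noncentrality is d√(n/2) = 1.06 × √7 = 2.8045, with 26 degrees of freedom. At an uncorrected two-sided 0.05:

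- exact t (critical value 2.056): 77.0%
- normal approximation: Φ(2.8045 − 1.9600) = 80.1%

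**Step 4: apply the Sidak correction.** The per-contrast level is α_m = 1 − 0.95^(1/m). Three assessment times suggest m = 2 (between-group contrasts at the two follow-up visits) or m = 3 (baseline included). These are illustrations, not values from the article.

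| Family size m | α_m | Exact t, 14 per group | Normal approx., 14 per group | Exact t, 20 per group (no loss) |
|---|---|---|---|---|
| 1 (no correction) | 0.0500 | 77.0% | 80.1% | 90.4% |
| 2 (assumed) | 0.0253 | 66.7% | 71.5% | 84.2% |
| 3 (assumed) | 0.0170 | 60.4% | 66.2% | 79.9% |

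For example, with m = 2 the normal approximation is Φ(2.8045 − 2.2365) = 71.5%; with m = 3 it is Φ(2.8045 − 2.3877) = 66.2%. A larger family, as would follow if within-group contrasts shared the correction, lowers power further: 55.8% at m = 4 by exact t with 14 per group.

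**Step 5: what 20 per group supports at an uncorrected 0.05.** 15 of 20 completing is a loss of 5/20 = 25%, and 15 per group gives 80.0% by exact t. So 20 per group gives 80% power with up to 25% drop-out, or 77% with 30%.

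**The case against.** The strongest reply is that nothing has been miscalculated. The 20 per group follows exactly from a standard formula, the three-point gap between 77% and 80% is only the exact t-test against the normal approximation, and 22 against 20 is a small difference. All of this stands. A reader might infer that the sample size is an arithmetic error; the article does not support that.

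Second, a reader might infer that the trial's power simply is 60–67%. The article does not support that either. It gives no family size. If the correction covers only time contrasts within groups, or is applied separately at each visit, where two arms give one between-group contrast, then m = 1 and Sidak costs nothing. The lower figures also require the full 30% loss, which is a planning allowance; with everyone observed, power is 84% for a family of two and 80% for three. These points stand, and the figures must be given as conditional.

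Third, the group-by-time effect in the ANOVA could be the primary test, and it carries no Sidak correction. That is a possible reading, but it does not rescue the stated figure: the power of that test depends on the within-person correlation between visits, which section 2.4 neither gives nor uses.

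Fourth, the primary contrast and the membership of a correction family are often left to an analysis plan, which is not shown here. That is fair as far as an omission goes. What remains is not an omission: the article itself states one test for sizing and another for analysis, and no sentence connects them.

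**Conclusion.** The point holds as a mismatch between sections 2.4 and 2.8. The stated 80% belongs to an uncorrected two-group test at 0.05 and has not been shown to be the power of the planned analysis.

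Its size depends on how section 2.8 is read. If the six-month contrast escapes correction, power with the planned loss is 77% (80% by the normal approximation), a minor shortfall. If it is corrected, power is about 67% (72%) for a family of two and 60% (66%) for a family of three. These figures assume a standardised effect of 1.06, a two-sided test, 14 completers per group and the family size named. The discrepancy should be resolved in the text, and no extra patients are needed to do so.

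**What to change.** Keep 80 patients. In section 2.8, name the between-group contrast at six months on the SF-36 physical-health domain, within each joint, as the single primary test at two-sided 0.05. State that it is not conditional on a significant omnibus ANOVA and carries no Sidak correction. Keep the Sidak and Bonferroni corrections for the other contrasts.

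In section 2.4, restate the power for that test as either about 77% with 30% drop-out (14 of 20 completing) or 80% with up to 25% drop-out (15 of 20 completing).

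The cost is a few sentences and a slightly less favourable power or drop-out statement. Recruitment, visits and measurements do not change.

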### 2.5. Description of Procedure and Randomization

Both THR and TKR patients will be randomly assigned to the intervention groups and control groups after the post-surgery rehabilitation after having revised inclusion/exclusion criteria again. A randomization list, defined by a generator of random numbers available on the Emilia-Romagna Region website (http://wwwservizi.regione.emilia-romagna.it/generatore/, accessed on 11 April 2021) surgical intervention, 40 numbers within the interval (1,40) will be generated.

### 2.6. Allocation, Concealment and Blinding

This is a single blind RCT study. Random assignment to intervention groups or control groups will be performed by personnel other than those who will perform clinical and functional assessments. The list of allocation of the patients to the groups will be kept locked and separated from the rest of the material used to collect patients’ information. At any time, professionals who perform motor assessments will not be aware of which group participants have been assigned. Participants will be clearly instructed not to reveal the trainer who performs the assessment to which exercise group they have been assigned.

#### 2.6.1. Intervention Groups (IGs)

The intervention groups for THR and TKR will be trained under the direct supervision of a graduate trainer in Sports Science. The protocol aims to reach fitness by improving muscular strength, range of motion (ROM), and muscular elasticity, as well as gait, balance and aerobic capacity. The exercise program is structured in 2 days per week 1 h sessions, and lasts six months. Each session is divided into warm-up, strength, balance, flexibility and cool-down sections. The protocol defines strategies to instruct patients and check the correct and safe execution of the motor tasks for both THR and TKR. 

The exercises are chosen to avoid potentially harmful or painful movements or positions according to the participants’ conditions. For instance, exercises in quadrupedal position are excluded for persons with TKR. Exercises with leg adduction movements and in lateral decubitus positions are excluded for persons with THR. In order to follow the progressive workload adapting criteria, frequency, type, time and duration of the training will be modified based on the functional capacity reached by participants. Only common-use low-cost tools, such as elastic bands, yoga mats, dumbbells and soft dumbbells, are used within the exercise sessions. 

In addition, all persons of the intervention groups will be requested to choose an additional third day of the week to carry out at least one of the following activities: brisk walking, cycling or swimming. The duration of these additional activities will be at least 30 min in order to reach the minimum amount of exercise per week of 150/300 min recommended by WHO [23]. Participants to the intervention group will be monthly request how many hours of additional activities has been done during the last month.

